## Abstract

**Background:**

Multiple sclerosis (MS) is a neurological disease of the central nervous system and is associated with many psychosocial symptoms that are difficult to manage including low mood, anxiety, fatigue and pain, as well as low health-related quality of life. Internet-based psychosocial interventions that use mindfulness-based approaches are gathering much attention in recent literature, particularly in the treatment of chronic illnesses. However, no large randomized controlled trials have been done examining the efficacy of such interventions for people with MS (PwMS).

**Methods/design:**

This study is a randomised controlled trial of an online mindfulness-based intervention (MBI) for PwMS. Participants will be randomised to receive either the MBI or offered the intervention after a waiting period. All participants will be assessed to determine whether they have a history of recurrent depressive disorder. The primary outcome will be severity of depression, according to the Centre of Epidemiology Depression Scale. Secondary outcomes will be anxiety severity, fatigue, pain and quality of life. Assessments will be conducted pre, post-treatment, at three and six-month follow-up. The online mindfulness-based program was developed in collaboration with end-users (*n* = 19 PwMS) who gave feedback about what would be feasible and acceptable, and the draft program was reviewed by both experts and patients.

**Discussion:**

Multiple sclerosis is the most common acquired chronic neurological disease amongst young adults and is associated with a range of symptoms that can be difficult to cope with. In face-to-face interventions, a MBI demonstrated the largest effect in a recent meta-analysis of psychological treatments for PwMS, but MBIs for PwMS have not been delivered online. Hence, this trial will confirm whether MBIs can be efficacious when delivered online. A range of symptoms are assessed as outcomes so that the nature of benefits associated with the online MBI can be ascertained.

**Trial registration:**

ACTRN12618001260213.

**Date of Registration:** 25/07/2018.

**Electronic supplementary material:**

The online version of this article (10.1186/s12883-019-1356-9) contains supplementary material, which is available to authorized users.

## Background

Multiple sclerosis (MS) is an autoimmune demyelinating disease of the central nervous system [1]. While it remains a clinical diagnosis, the diagnostic criteria for MS has evolved over the decades and recent iterations have been more influenced by radiological findings, namely the identification of lesions or plaques in the brain and/or spinal cord in a particular distribution and with certain features [2]. The 2017 McDonald Criteria for MS are the most recent diagnostic criteria, and radiological features have been incorporated to allow an earlier diagnosis of MS than with earlier versions of the diagnostic criteria [2]. People with MS (PwMS) have a range of psychosocial consequences and symptoms associated with the illness that compromise their quality of life. These include depression, anxiety, fatigue and pain. The most commonly used psychosocial approach to improve coping with these symptoms is Cognitive Behaviour Therapy (CBT). Early meta-analyses found that CBT is effective for improving mood [3–5], fatigue [6], and health-related quality of life (HRQoL) [7] in PwMS. However, these meta-analyses included relatively few studies, most with small sample sizes (e.g. *n* < 20 per study arm) which may over-estimate treatment efficacy [8]. Some only included studies that pre-screened for low mood [3, 4]. A more recent, comprehensive meta-analysis examined the efficacy of psychosocial interventions for PwMS [9] and found that CBT was not effective in improving anxiety, depression, fatigue or HRQoL in PwMS, when considered in isolation, in contrast to other interventions.

From the most recent meta-analysis, the intervention with the largest effect sizes for depression (*d* = 0.8) and anxiety (*d* = 0.6) in PwMS was an 8-week mindfulness-based approach [10], which was based on Jon Kabat-Zinn’s mindfulness-based stress reduction (MBSR) program [11]. This intervention also produced moderate effects for fatigue (*d* = 0.5) and HRQoL (*d* = 0.6) in PwMS, suggesting that a mindfulness program may be an appropriate psychosocial intervention to investigate as an adjunctive treatment to the medical management of MS.

Studies have shown that mindfulness-based interventions, such as MBSR, are efficacious for a wide spectrum of chronic disorders including fibromyalgia [12], rheumatoid arthritis [13], coronary artery disease [14], cancer [15], chronic pain [16], chronic fatigue [17] depression and anxiety [18]. However, Grossman and colleagues’ [10] study is the only published randomized controlled trial that examined the effect of mindfulness-based interventions for PwMS on a range of health outcomes including depression, anxiety, fatigue, pain and quality of life. This high quality randomized controlled trial had a relatively large sample of 150 PwMS. It was delivered face-to-face and it was intensive (27 hrs in total). For many PwMS, such a lengthy program would be difficult to access for a variety of reasons including work status, rurality, financial barriers and/or disability. Indeed, due to the chronic and potentially disabling nature of MS, frequent or regular travel can be difficult. Numerous previous studies have relied upon psychological interventions being provided over the telephone [19–21] or via teleconference [22]. Furthermore, a 2015 survey of over 2800 PwMS found that there was a considerable unmet psychological need to optimise the accessibility of psychological services and support [23].

One mode of treatment delivery that may be easily transferable to clinical practice, but which is yet to be fully explored for PwMS, is Internet-delivered therapy. There is considerable evidence that online interventions guided by a therapist result in improvements that are equivalent to face-to-face formats for a range of mental and physical health problems [24]. So far, there are three trials investigating the efficacy of online psychological interventions for PwMS. All three have used a cognitive-behavioural approach. The first was a proof of concept trial (*n* = 24), called “Beating the Blues” [25] which reported a number of difficulties including a low recruitment rate and no outcome data were reported. The "MS Invigor8" trial, [26] was also a pilot (*n* = 40), but reported preliminary outcome data and found improvements in fatigue, anxiety, depression, quality of life, as well as good acceptability of the online program. The "Deprexis" trial, by Fischer et al., (2015) was a larger RCT (*n* = 90) [27] that evaluated a standard iCBT protocol for depression in PwMS. They found significant improvements in depressive symptoms but not in the disease-specific quality of life measure, and only the psychological well-being subscale of a general quality of life scale. Fischer and colleagues reported that participants indicated the need to tailor the program to MS-specific needs. The authors also speculated that their treatment effects may have been enhanced by the inclusion of therapist support. Taken together, these online CBT studies indicate that Internet-delivered psychosocial interventions for PwMS may be an acceptable and viable option for PwMS.

Whilst CBT is considered to be the “gold standard” psychological therapy for a range of psychological indications associated with MS, our meta-analysis [9] identified that CBT may not be an optimal approach for PwMS. CBT is typically a short-term intervention, and relies on the ability to think analytically, focusing on identifying and challenging unhelpful beliefs. These skills may be suboptimal for those with cognitive impairment, which is often apparent in PwMS (ranging from 43 to 70%, depending on the setting [28]). In contrast, mindfulness-based interventions involve the long-term practice of meditation, but focus on the development of a single skill (i.e. cultivating a moment-to-moment awareness of the present moment), which may be more appropriate for people with MS and concomitant cognitive decline. Furthermore, these “mind-body” interventions, involving “body-based”, experiential learning promote acceptance and the development of an increased tolerance (or desensitization) to difficult thoughts, emotions and sensations, which may be more suited to PwMS who are faced with the unrelenting challenges of adjusting to life with an irreversible and progressive chronic illness.

### Aims and hypotheses

The aim of the current study is to evaluate the efficacy of an online mindfulness-based program for symptoms of depression, anxiety, fatigue, pain and health-related quality of life in PwMS. Whilst mindfulness is a centuries-old tradition stemming from Buddhist philosophy, the current scientific interest in mindfulness as a treatment for mental health problems started as a method to prevent depressive episodes in people with a history of depression who were currently asymptomatic. Evidence supports the efficacy of mindfulness for the prevention of recurrence of depression [29]. Since a large proportion of PwMS develop major depression (50% lifetime prevalence [30]), the ability of mindfulness to prevent future relapse of depression amongst those with a history of depression may be particularly valuable in the management of PwMS. Furthermore, whilst Grossman et al. (2010) did not examine depressive disorders or relapses of depression, there is evidence in the rheumatoid arthritis (RA) literature that while CBT was more effective overall than MBSR, for those patients who had a history of recurrent depression (two or more episodes), mindfulness outperformed CBT [31]. Given that the prevalence of clinically significant depression in people with rheumatoid arthritis is estimated to be approximately 16% [32] and the rate is considerably larger for PwMS, the potential benefits of mindfulness may be greater in MS. Therefore, a secondary aim of this study is to determine whether PwMS with a history of recurrent depression will benefit significantly more from the online mindfulness program than those without. We define recurrent depression as having two or more episodes of depression, consistent with work in RA [31]. If there are insufficient numbers to test the recurrent depression hypothesis, we will examine whether having any history of lifetime depression (current or history) is a moderator of treatment effect. To elucidate the likely mechanisms of treatment gains, we will examine whether changes in the state mindfulness will mediate the effect between treatment group and treatment outcomes, and whether adherence to mindfulness practice predicts outcome in the treatment group.

We hypothesize that **(1)** PwMS who participate in the online mindfulness intervention will demonstrate significant improvements in depressive symptoms (primary outcome), anxiety, fatigue, pain and HRQOL outcomes at post-treatment, 3-month, and 6-month follow-up, compared with waitlist controls; **(2)** PwMS with a history of recurrent depression will benefit significantly more from the online mindfulness program than those without; **(3)** Changes in mindfulness will mediate the effect between treatment group and treatment outcomes; **(4)** PwMS that report greater meditation adherence will have greater improvements in outcomes than those without.

## Methods/design

The current study will be a CONSORT-R compliant [33] randomized controlled trial (RCT) and is registered with the Australian New Zealand Clinical Registry (ACTRN12618001260213). Ethics approval has been granted by the University of Sydney Human Research Ethics Committee (Project No. 2018/402). Please see Fig. 1 for an illustration of the trial procedure.

**Fig. 1 Fig1:**
[figure not shown]
Outline of study design. TICS; Telephone Interview for Cognitive Status, PRIME-MD; Primary Care Evaluation of Mental Disorders- Major Depression Module, PDDS; Patient Determined Disease Steps, PHQ-9; Patient Health Questionnaire, CES-D; Centre for Epidemiological Studies of Depression, GAD-7; Generalized Anxiety Disorder 7-item scale, FSS; Fatigue Severity Scale, BPI-SF; pain intensity and interference from the Brief Pain Inventory- Short Form, MSIS-29; Multiple Sclerosis Impact Scale, CAMS-R; Cognitive and Affective Mindfulness Scale- Revised

### Participants

People with MS will be included in this study if they (1) report a neurologist-confirmed diagnosis of MS (2) ≥ 18 years old (3) currently live in Australia (4) have regular access to the Internet (5) have sufficient English to complete questionnaires and understand program content in English (6) if taking MS treatment, are on a consistent MS regimen for > 1 month (7) if taking anti-depressant medication, are on a stable dose for > 8 weeks. Participants will be excluded if they have (1) a comorbid medical condition known to impact on cognition or physical ability (2) moderate-severe cognitive deficits (< 25 on the Telephone Interview for Cognitive Status; TICS [34]) (3) suicidal intent requiring emergency care (4) alcohol or drug abuse or dependence (5) a psychotic illness (6) received consistent psychotherapy within the last 6 months (7) are pregnant.

Participants will be recruited from the Multiple Sclerosis Clinic at the Brain and Mind Centre, the University of Sydney (Sydney, Australia), by (1) contacting patients that expressed interest in being involved in “future mindfulness-based studies” as part of a previous qualitative study; and (2) approaching consecutive patients face-to-face. In addition, the study will be advertised by Multiple Sclerosis Research Australia via newsletters and clinical trial websites, through flyers posted at the MS Society, as well as in Multiple Sclerosis Facebook support groups.

### Procedure

Participants that have registered interest in the study will be contacted using contact details provided on an online form. A pre-trial telephone interview will be conducted by a registered psychologist (supervised by clinical psychologist, LS) to establish eligibility for the study. Participants that meet criteria will undergo a telephone-administered clinical interview, the Primary Care Evaluation of Mental Disorders- the Major Depression Module (PRIME MD; [35]) to determine those with a history of lifetime depression and those without. PwMS that indicate that they have suicidal intent and require emergency care will be referred to the appropriate mental health service according to a suicide risk assessment decision tree and will not be eligible to participate.

Participants will be given information about the study over the phone and online. They will also be able to provide consent to the study online, and will be sent the Participant Information and Consent forms (see Additional file 1) via e-mail for personal record-keeping. Those that consent will be automatically directed to demographic and baseline questionnaires (Patient Health Questionnaire; PHQ-9 [36]; Centre for Epidemiological Studies of Depression; CES-D [37]; Generalized Anxiety Disorder Scale; GAD-7 [38]; Fatigue Severity Scale; FSS [38]; Pain intensity and interference from the Brief Pain Inventory- Short Form; BPI-SF [39]; Multiple Sclerosis Impact Scale; MSIS-29 [40]; 10-item Cognitive and Affective Mindfulness Scale- Revised; CAMS-R [41]). Upon completion, randomisation will be conducted by an independent researcher into either the 8-week mindfulness-based intervention or a waitlist control group. Participants will then be contacted by a member of the research team and informed of their randomised condition.

Participants allocated to the mindfulness-based intervention will receive five modules (approx. 15 mins in length), followed by a multiple-choice module quiz (approx. 1 min), over 8 weeks (1 module per 1–2 weeks) and five accompanying meditation audio-guides. They will also be guided by 5–8 × 10-min telephone calls (approx. 1 per week) with a registered psychologist to (1) encourage participation (2) normalize challenges to treatment (3) help resolve any technological difficulties. Participants allocated to the waitlist group will not receive the intervention, but will continue having treatment as usual, and will be asked to complete all demographic and outcome questionnaires. All participants will complete the Patient Health Questionnaire (PHQ-9 [36]) at baseline and every week online, throughout the course of the trial, as well as at post-intervention, 3-month and 6-month follow- up) to monitor mood and suicide risk. Post-intervention questionnaires will be administered to all participants at post-intervention (Week 9), at 3-month follow-up (Week 21) and at 6-month-follow-up (Week 33). Those who do not complete will be contacted by email and/or telephone up to three times in order to remind them complete their questionnaires.

### Randomisation

Randomisation will be stratified by history of major depression (assessed via the PRIME-MD). This will be performed by a researcher who will have no contact with participants throughout the duration of the trial, using computer-generated random numbers.

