### Outcome measures

The primary outcome measure will be depressive symptoms, as measured by the CES-D [37]. The secondary outcomes will include depressive symptoms (PHQ-9), and will be measured online, at baseline, Weeks 1- Week 8, at post-intervention, 3-month and 6-month follow up. All other secondary outcomes, including anxiety (GAD-7 [38]); fatigue (FSS [38]); pain (BPI-SF; [39]), and MS-related Quality of Life (MSIS-29 [40]) and the primary outcome will be measured online at baseline, post-intervention, 3-month and 6-month follow-up.

To investigate factors that may affect treatment success, we will also be measuring several process outcomes. A measure of mindfulness (CAMS-R 10-item [41]) will be administered to all participants at baseline, post- intervention, 3-month and 6-month follow-up in order to investigate whether changes in mindfulness will mediate the relationship between treatment group and treatment outcomes. At post-intervention (Week 9), participants will also be asked to answer online questions about any changes to treatment during the past eight weeks, including whether they started or changed any disease-modifying MS treatments, started seeing a psychologist/ psychiatrist, began or changed the dose of any new mood stabilizing treatments. Participants in the intervention group will complete additional therapy adherence questions (i.e. the type, frequency, and duration of mindfulness meditation) at the end of each week, at 3 and 6-month follow-up. Those in the intervention group will also complete the Credibility/Expectancy questionnaire [42] at the end of Week 1 and questions regarding treatment satisfaction during the last week of the program (Week 8).

The demographic questionnaire administered at the outset of the trial will include questions about patient characteristics (e.g. age, gender, employment status), disease characteristics (e.g. type, duration of MS), current MS-related and mood-stabilizing treatments, and previous experience with psychological therapy and mindfulness meditation. Confirmation of MS diagnosis and type of disease course will be obtained with participants’ permission from their neurologist. The Patient Determined Disease Steps (PDDS) questionnaire [43] will also be administered as part of the demographic data, as a measure of self-reported disability in order to determine whether level of disability moderates treatment outcome.

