### Statistical analysis

Data will be analysed using intention-to-treat analysis [44]. There are four measurement times, of which three are post-intervention. Linear mixed models will be generated with group as the fixed factor and baseline level of each treatment outcome (e.g. CES-D, GAD-7) as the covariate. Multiple linear regression analyses will also be used to predict change in outcomes over treatment and to investigate the predictive value of potential moderators (i.e. type of MS, depression, fatigue and pain status). Missing data will be minimized using a forced online completion format and participants who are willing will be asked to complete questionnaires even if they drop-out from the online program. Reporting will follow the CONSORT statement [33]. For further information on data management and security, please see Additional file 1.

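### The stated efficacy model omits the randomisation stratum (history of major depression), giving up a little precision that one extra model term would recover

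*Protocol article*

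**What the plan says.** **Design.** The Randomisation section states: "Randomisation will be stratified by history of major depression (assessed via the PRIME-MD"). It adds that a researcher with no participant contact uses computer-generated random numbers. Blocking, or any other way of keeping the arms balanced within strata, is not described.

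**Interview.** The Procedure section says the PRIME-MD interview is used "to determine those with a history of lifetime depression and those without".

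**Efficacy model.** The Statistical analysis section specifies linear mixed models "with group as the fixed factor and baseline level of each treatment outcome (e.g. CES-D, GAD-7) as the covariate". The stratification factor is not among the named terms.

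**Other use of depression.** The same section plans multiple linear regressions to "investigate the predictive value of potential moderators (i.e. type of MS, depression, fatigue and pain status"). These are separate from the between-group models.

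**Primary outcome.** Under Outcome measures: "The primary outcome measure will be depressive symptoms, as measured by the CES-D".

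**The concern.** The trial randomises within groups defined by depression history and then, as written, analyses as though those groups did not exist. Depression history is a plausible predictor of a later depression score, and the Aims and hypotheses section itself expects history to matter for response. Variance between strata that the model could remove stays in the residual.

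Two consequences should be kept apart:

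- **Lost precision.** If the stratum predicts outcome beyond baseline CES-D, the comparison is less precise than it could be, however the randomisation list was made.
- **Miscalibrated standard errors.** If the arms are also balanced within strata, the true sampling variance of the treatment difference excludes the stratum effect, but the model's standard error still includes it. Intervals are then too wide and the test rejects less often than its nominal level.

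At stake is a modest loss of efficiency. The validity of the result is not in question.

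**Working it through.** **The plan's own figure.** The article gives no figure for this point. The nearest is the total of 125 with 20% drop-out, which leaves 125 × 0.8 = 100 completers. The stated 80% power is used below only as a nominal reference. The 125 itself was not reproduced: a two-sided two-sample comparison at d = 0.3 to 0.2 needs 350 to 786 before drop-out. That is a separate matter and does not affect this point.

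**Inputs**

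- Model terms: group and own baseline (Statistical analysis).
- Stratum: history of major depression, yes/no (Randomisation and Procedure).
- Stratum split for the simulation: 50/50, from the background figure, "Since a large proportion of PwMS develop major depression (50% lifetime prevalence [30"]).
- Alpha 0.05 (Sample size), taken as two-sided because sidedness is not stated.
- R² = share of residual outcome variance explained by the stratum after baseline adjustment. The document does not give it, so a range is assumed.

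**Formulas, allocation balanced within strata**

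- Ratio of stated-model to adjusted standard error: k = 1/√(1 − R²)
- Actual type I error: 2 × [1 − Φ(1.96k)]
- Actual power when the adjusted model has 80%: 1 − Φ(1.96k − 2.80), where 2.80 = 1.96 + 0.84

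| R² (assumed) | k | Interval wider by | Type I error | Power |
|---|---|---|---|---|
| 0 | 1.000 | 0% | 0.050 | 80.0% |
| 0.01 | 1.005 | 0.5% | 0.049 | 79.7% |
| 0.02 | 1.010 | 1.0% | 0.048 | 79.4% |
| 0.05 | 1.026 | 2.6% | 0.044 | 78.5% |
| 0.10 | 1.054 | 5.4% | 0.039 | 76.9% |

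**Allocation not balanced within strata.** The standard error is then correct for the model fitted, and type I error stays near 0.05. The widening factor k applies to real sampling error, so power is about 1 − Φ(1.96 − 2.80/k). At R² = 0.01, 2.80/1.005 = 2.79, giving 79.6%. At R² = 0.10, 2.80/1.054 = 2.66, giving 75.7%. Adding the term recovers slightly less than this difference, because chance imbalance in the stratum has its own small cost.

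**Simulation check.** Settings: 100 completers, two equal strata, baseline slope 0.6, a 0.6 SD baseline gap between strata, 6,000 runs per setting, balanced allocation. Power is at d = 0.45.

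| Extra stratum effect | Mean SE without / with stratum | True SD of estimate without stratum | Type I error without stratum | Power without / with stratum |
|---|---|---|---|---|
| 0.2 SD | 0.156 / 0.155 | 0.153 | 0.045 | 82.0% / 82.4% |
| 0.4 SD | 0.151 / 0.146 | 0.145 | 0.040 | 84.7% / 86.4% |
| 0.6 SD | 0.145 / 0.133 | 0.135 | 0.036 | 88.8% / 91.8% |

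With the stratum in the model, type I error was 0.046 to 0.048. On the R² scale these settings are roughly 1 − (0.155/0.156)² = 0.01, 1 − (0.146/0.151)² = 0.07 and 1 − (0.133/0.145)² = 0.16, so the third lies outside the range used for the conclusion.

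Without balanced allocation, at an extra effect of 0.4 SD, the mean SE without the stratum was 0.152 and so was the true SD. It was 0.147 with the stratum. So calibration is sound there and only precision is lost.

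**Cost of adding a useless term.** With no extra stratum effect and no balancing, mean SE went from 0.1612 to 0.1620, a ratio of 1.005. That is about half a percent.

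**The case against.** **The model sentence is abbreviated.** It names no time term, no group-by-time term and no random effect, although there are three post-intervention measurements. Silence about the stratum is therefore weaker evidence of exclusion than it would be in a full model statement, and an analysis plan that is not shown may add it. This stands as a limit. But the article does choose to name the adjusting covariate, and it places depression elsewhere, in separate moderator regressions.

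**Baseline already does much of the work.** Baseline CES-D absorbs part of what history predicts, so R² may be small. At R² near 0.01 without balanced allocation, the gain and the cost of the extra term roughly cancel. This stands, and it is why the point is minor. Each secondary model adjusts only for its own baseline, so those models have no direct depression term; how far history predicts fatigue, pain or MSIS-29 is unknown.

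**Stronger readings that the document does not support.**

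- A reader might infer that the published intervals will definitely be too wide. That requires balance within strata, and the article says only that randomisation is stratified and uses random numbers.
- A reader might infer bias or a false-positive risk. Neither follows: the error, where there is one, is conservative.
- A reader might infer that Hypothesis 2 lacks its variable, because the stratum is any lifetime depression while the Aims say "We define recurrent depression as having two or more episodes of depression". The Abstract says every participant is assessed for recurrent depressive disorder, and the Aims give a fallback to any lifetime depression if numbers are too few. A moderator need not be a stratification factor, and three strata in 125 participants would be a trade-off, not a clear gain.

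**Conclusion.** The point holds as a minor one. As written, the analysis does not carry the factor by which participants are randomised. The certain consequence, if history is prognostic beyond baseline, is some lost precision. Conservative standard errors follow only if allocation is also balanced within strata.

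The size rests entirely on the assumed R². For 1% to 10%, the cost is about 0.5% to 5% of interval width, and power moves from a nominal 80% to between about 79.7% and 76.9% under balanced allocation. For zero there is no loss. The treatment estimate remains unbiased throughout.

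**What to change.** Add history of major depression, coded exactly as used at randomisation, as a fixed effect in the CES-D model and in the between-group models for the secondary outcomes. State this before outcome data are examined. If a separate analysis plan already includes the term, no change is needed beyond making the documents agree.

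The cost is one model term and about one degree of freedom, with no new data: the value is already collected before randomisation. If the factor proves unrelated to outcome, the standard error rises by about half a percent at most in the simulated setting.
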